### Confidentiality {27}

At the time of randomisation, participants will be assigned a trial ID number which will be used on all the personal information containing documents (e.g. paper CRF and eCRF). The Code Key will be kept in a safe where only the trial investigators have access. The coded information will be kept in an electronic database or in a folder in a locked document cabinet. When data from the study is published, personal data will not be identifiable.

### Plans for collection, laboratory evaluation and storage of biological specimens for genetic or molecular analysis in this trial/future use {33}

We have no plans to collect or store biological specimens in the current or future ancillary studies.

## Statistical methods

### Statistical methods for primary and secondary outcomes {20a}

#### Primary outcome

We will analyse VFD as a continuous outcome between two groups with a non-normal distribution using the Mann Whitney *U* test. We will provide the absolute median difference in VFD between groups with 95% confidence intervals (CI). We will also calculate and present the Mann-Whitney (ϕ) parameter with 95% CI using the R function wmwTest in the asht R package as suggested by Fay et al. [21]. We will also perform a sensitivity analysis of the primary outcome using unadjusted competing risks regression [14]. We hypothesise that the intervention group (Helmet CPAP) will have a significantly (*p* < 0.05) higher VFD than the control group (HFNC).

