## Trial design {8}

Investigator-initiated, randomised, controlled, investigator-blinded, pragmatic superiority trial with a parallel group design, 1:1 concealed allocation ratio and a 28-day main follow-up period.

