### Outcomes {12}

#### Primary outcome

Ventilator-free days (VFD) within 28 days after randomisation. Patients who die within 28 days will be counted as 0 VFD. Time in ventilator will be counted in hours and rounded to whole days (continuous data).

Secondary outcomes:
SpO2/FiO2 ratio assessed 1 h after randomisationPatient comfort 1–10 (visual analogue scale) assessed 24 h after randomisationFrequency of endotracheal intubation within 28 days from randomisationFrequency of carbon dioxide rebreathing (pCO2 > 6 kPa in a VBG) within 28 days from randomisationDays alive within 28 days from randomisationDays alive within 180 days after randomisation (not in primary publication)

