**Fig. 1 Fig1:**
[figure not shown]
Participant timeline. Patients in the medical intermediate COVID-19 cohort ward will be screened for eligibility according to the inclusion and exclusion criteria, given written and oral information and then asked for written informed consent. Secondary endpoints will be collected at 1 h, 24 h and 28 days from randomisation, when the primary endpoint of ventilator-free days will also be assessed. We plan to include 60 patients in each group and expect the HFNC group to have ~ 19.5 VFD and the Helmet CPAP group to have ~ 23.3 VFD at 28 days. The thickness of the lines corresponds to the expected patient density in intervention versus control group and treatment in ward versus intensive care and in patients who survive or die within 28 days from randomisation. Abbreviations: SpO2, peripheral oxygen saturation; FiO2 ratio, fractional inspired oxygen concentration; RR, respiratory rate; PEEP, positive expiratory end-pressure; NEWS, national early warning score; AE, adverse events; VFD, ventilator-free days (within 28 days); ICU, intensive care unit; CPAP, continuous positive airway pressure

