### Sample size {14}

We have estimated a required sample size of 120 patients (60 per group) to achieve 90% power to detect superiority at a 0.05 significance level. This estimate is based on the following clinical assumptions and statistical calculations:
A median of 1 out of 3 patients started on HFNC or Helmet CPAP will be started on invasive mechanical ventilation [2].Patients put on the ventilator will be treated in the ward for median 2.3 days before intubation, and ventilated patients will have 67.4% ICU mortality, and those who survive will stay on the ventilator for a median of 6 days [13].Patients not put on the ventilator will have 8.1% 28-day mortality and survive for a median of 7.5 days [2].The Helmet CPAP will avoid 3 out of 5 intubations compared to HFNC, which is an estimate based on (A) Frat et al. [4] who reported 40/106 (38%) intubation frequency in HFNC treated patients with AHRF versus 55/110 (50%) in patients with CPAP masks (*p* = 0.18 for comparison) and (B) Patel et al. [9] who reported 24/39 (61.5%) intubation frequency in patients with ARDS treated with CPAP mask versus 8/44 (18.2%) treated with Helmet CPAP (*p* < 0.001 for comparison). Hence, we expect treatment with Helmet CPAP to require (18.2/61.5)/(38/50) ≈ 2 out of 5 intubations compared to HFNC.

This leads to an estimated VFD of 19.545 for patients on HFNC (calculation: ((2/3*0.919*28) + (1/3*0.326*22))) and 23.257 for patients on Helmet CPAP (calculation: ((13/15*0.919*28) + (2/15*0.326*22))). We assume the standard deviation (SD) to be 6 in both groups based on a mean estimate of SDs reported from five trials with VFD as the primary endpoint in the paper by Yehya et al. [14]. Because we expect a reduction of intubation frequency and days in ventilator to be the driving factor behind a reduction in VFD rather than mortality, we will use Mann-Whitney *U* test as the primary statistical method, also based on argumentation by Yehya et al. [14]. In order to estimate the sample size, data was simulated with mean 23.257 for the intervention group and mean 19.545 for the control group, the standard deviation was set to 6 for both groups, and then the sample size was varied by simulation until the proportion of significant (0.05) two-sided Mann-Whitney *U* test was equal to the desired power (0.90) using R statistical software (See Additional file 1 for R code). This resulted in a required sample size of 60 patients per group.

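### One of the two effect estimates planned for the primary outcome, the median difference in ventilator-free days, is expected to be 0 under the protocol's own assumptions

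*Protocol article*

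**What the plan says.** The primary outcome is "Ventilator-free days (VFD) within 28 days after randomisation", with the rule "Patients who die within 28 days will be counted as 0 VFD". The scale is therefore bounded at 0 and 28.

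Statistical methods {20a}, Primary outcome, tests VFD with the Mann-Whitney U test and names two effect estimates. The first: "We will provide the absolute median difference in VFD between groups with 95% confidence intervals (CI". The second, in the next sentence, is the Mann-Whitney parameter with a 95% CI. A competing risks regression is planned as a sensitivity analysis.

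The expected effect is expressed as a difference in means. The Fig. 1 legend says the authors "expect the HFNC group to have ~ 19.5 VFD and the Helmet CPAP group to have ~ 23.3 VFD at 28 days", and Sample size {14} derives both figures as weighted averages. {20a} names no estimate of that mean difference.

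**The concern.** The averages in Sample size {14} give every never-ventilated survivor 28 days. If such patients form more than half of each arm, the median of each arm is the ceiling value, and the difference in medians is 0 whether or not the helmet prevents intubations. This comes from the estimand, so a larger sample would not cure it.

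What is at stake is how the primary result reads. The median difference is the only effect estimate on VFD in {20a} that is in days. A trial that succeeds as planned could publish p < 0.05 beside a difference of 0 days, and readers could take that as no effect or as a contradiction. Choosing another day-scale estimate after seeing the zero would look post hoc.

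**Working it through.** **Inputs, all from Sample size {14} unless noted.** HFNC intubation is 1/3 ("A median of 1 out of 3 patients started on HFNC or Helmet CPAP will be started on invasive mechanical ventilation"). Helmet intubation is 2/5 of that, or 2/15. Survival is 0.919 if not ventilated (28 VFD) and 0.326 if ventilated (22 VFD). Deaths score 0 (Outcomes {12}). There are 60 per group.

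**1. The plan's own figures.**
- HFNC mean: 2/3 × 0.919 × 28 + 1/3 × 0.326 × 22 = 17.155 + 2.391 = 19.545.
- Helmet mean: 13/15 × 0.919 × 28 + 2/15 × 0.326 × 22 = 22.301 + 0.956 = 23.257.
- Difference: 3.7 days.
- The plan states a "required sample size of 120 patients (60 per group) to achieve 90% power". Simulating normal data with these means and SD 6 gives Mann-Whitney power of 0.907 at 60 per group, so the figure reproduces. The normal shape is an assumption, because the R code is in a file not shown.

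**2. The outcome mix behind those means.**

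| VFD | HFNC | Helmet |
|---|---|---|
| 28 | 2/3 × 0.919 = 0.613 | 13/15 × 0.919 = 0.796 |
| 22 | 1/3 × 0.326 = 0.109 | 2/15 × 0.326 = 0.043 |
| 0 | 0.279 | 0.160 |

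The last row gives 60 × (0.279 + 0.160) ≈ 26 deaths, which agrees with the event count in the additional analyses section {20b}.

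**3. Population medians.** Both shares at 28 exceed one half, so both medians are 28 and the true difference is 0. Placing all ventilated survivors at 22 is a simplification, but spreading them below 28 would not change the shares at 28.

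**4. Difference of sample medians.** The median of 60 values is 28 when at least 31 of them are 28. The binomial probability is 0.950 for HFNC and above 0.9999 for helmet, so both medians are 28 with probability 0.950. In 20,000 simulated trials the difference was 0 in 95%, and in about 92% of those with a significant Mann-Whitney test.

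**5. Hodges-Lehmann reading.** For helmet minus HFNC pairs:
- positive: 0.7965 × (0.1087 + 0.2787) + 0.0435 × 0.2787 = 0.321
- tied: 0.7965 × 0.6127 + 0.0435 × 0.1087 + 0.1601 × 0.2787 = 0.537
- negative: 1 − 0.321 − 0.537 = 0.142

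The median pairwise difference is 0. The estimate was 0 in 99.9% of 4,000 simulated trials.

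**6. Mann-Whitney parameter.** 0.3206 + 0.5373/2 = 0.589, against 0.5 for no effect.

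**7. Interval for the median difference (percentile bootstrap).** It included 0 in every simulated trial. It was not usually narrow when the test was significant: the upper limit was 6 days or more in about 72–75% of those trials, and exactly 0 in about 17–18%.

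**8. Sensitivity to HFNC intubation, helmet at 2/5 of it.**

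| HFNC intubation | Share of HFNC at 28 | P(both sample medians = 28) |
|---|---|---|
| 1/3 (planned) | 0.613 | 0.95 |
| 38% (the HFNC rate also cited in {14}) | 0.570 | 0.83 |
| 45% (assumed for range) | 0.505 | 0.48 |

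The HFNC population median leaves 28 only above 1 − 0.5/0.919 = 45.6% intubation.

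**9. Precision of a mean difference.** The mix implies SDs of 12.28 and 10.23. SE = √(12.28²/60 + 10.23²/60) = 2.06, so the 95% half-width is 1.96 × 2.06 ≈ 4.0 days. A bootstrap interval for the mean difference included 0 in about 22–24% of trials with a significant Mann-Whitney test. These SDs differ from the 6 used for the sample size; that is a separate question, not pursued here.

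**The case against.** The strongest reply is that the plan already contains the right estimate. The Mann-Whitney parameter belongs to the test, comes with a CI, and moves off 0.5 under the planned effect. Intubation frequency and 28-day survival, which drive VFD, are secondary outcomes with their own analyses, and a competing risks regression is planned as well. A reader might infer that the trial would be left without a usable measure of effect. The document does not support that. What stands is narrower: the parameter is a probability, cannot be set against the 19.5 and 23.3 days of the planning section, and is not ranked above the median difference.

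A reader might also infer that the interval would collapse onto zero. It would include 0, but in most significant trials its upper limit is 6 days or more.

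Nor is a zero certain. It depends on HFNC intubation near 1/3, and at the 38% also cited in {14} the probability is 0.83. Above about 45.6% the HFNC median leaves the ceiling, though in this mix it can then only jump between 28, 22 and 0.

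Finally, a mean difference has its own mismatch with a rank test, since its interval can cover 0 when the test is significant. That is a fair reason to add it as a supporting estimate and not to treat it as the measure paired with the test.

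**Conclusion.** The point holds for one of two planned estimates. Under the protocol's own outcome mix the true median difference is 0 while the assumed mean gain is 3.7 days. With 60 per group the estimate is 0 in about 95% of trials as a difference of sample medians, and almost always as a Hodges-Lehmann shift. The first figure rests on 1/3 HFNC intubation, 8.1% mortality without ventilation, and the assumed helmet effect. It drops to 0.83 and 0.48 at 38% and 45% HFNC intubation.

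It would be a mistake to conclude that the primary test or its p-value is invalid; neither depends on the median difference. The consequence is a headline number in days that probably shows nothing, beside a test and a parameter that may show an effect. It should be fixed before the results are known, but it is not critical.

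**What to change.** In {20a}, or in the statistical analysis plan if there is one:

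- Name the Mann-Whitney parameter with its 95% CI as the main effect measure paired with the test.
- Report the difference in mean VFD with a bootstrap 95% CI in place of, or ahead of, the median difference, labelled as a supporting estimate on the scale used in {14}.
- Tabulate the proportions at 28, 1–27 and 0 days in each arm.

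The cost is a few sentences and a short bootstrap, with no new data and no change to the test. The downside is that the mean-difference interval is wide (half-width about 4 days) and can include 0 beside a significant rank test. The text should say so in advance. The change should be dated before outcome data are extracted for analysis.

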#### Secondary outcomes

SpO2/FiO2 ratio (a) and patient comfort (b) will also be analysed as continuous outcomes between two groups with the Mann Whitney *U* test. Frequency of endotracheal intubation (c) and carbon dioxide rebreathing (d) are dichotomized outcomes between two groups and will be analysed using a chi-squared test (unless groups are less than 5, then we will use Fisher’s exact test). Days alive within 28 (e) and 180 days (f) from randomisation will be visualised using a Kaplan-Meier plot and analysed using unadjusted Cox regression. We will test proportional hazards assumption using a global test, Schoenfeld residuals, and a log-log plot of survival. We will use Stata MP 16.1 statistical software.

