#### Outcomes rational

Based on the best current evidence [4, 9], we expect any difference in efficacy between intervention and control to be due to a difference in intubation rate and/or possibly time in respirator rather than survival. Respirator use is a particularly clinically relevant outcome during the current COVID-19 pandemic when ICU beds are scarce. The benefit of choosing VFD as a primary outcome rather than intubation frequency is that VFD strongly penalises death. Hereby, VFD effectively assesses our primary concern for harm related to the intervention, namely, an adverse delay to intubation leading to reduced survival. The drawback of VFD is a potential dilution of harm (death) due to high efficacy (intubation rate) which is why we are also including days alive within 28 and 180 days as secondary outcomes. The 180 days mortality outcome will not be reported in the primary manuscript because we do not wish to delay dissemination of findings, but we consider it necessary to evaluate since many patients with COVID-19 have prolonged hospital stay. SpO2/FiO2 ratio is included as a sort of proof of concept outcome with the purpose of confirming or rejecting our underlying assumption that the higher PEEP enabled by the Helmet CPAP will improve lung aeration. We also have a patient-centred outcome regarding self-reported comfort. Both devices are reported to have superior tolerance compared to low-flow oxygen therapy and CPAP masks but they have never been tested head-to-head in adults. Device comfort may be particularly important if the trial does not show superiority or if the effect size is small. Lastly, we have included a secondary outcome on carbon dioxide rebreathing which, according to our judgement, is the main harm apart from death and comfort/tolerance issues that can be considered more likely for the intervention group than the control group. We are taking measure to avoid this from happening (i.e. minimum Helmet CPAP air flow 40 L/min).

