### Data management {19}

Screening and baseline data will be entered live using an eCRF at the time of randomisation. Further data on primary and secondary outcomes will be entered into the REDCap database collectively after all patient recruitment has finished, using filled-out paper CRFs and electronic health records. Individual patient data will be handled as ordinary chart records and will be kept according to the European General Data Protection Regulation (GDPR). All original records (e.g. consent forms and CRFs) will be retained at the Department of Infectious Disease in Helsingborg Hospital for 15 years to allow inspection by relevant authorities. The coded trial database will be maintained for 15 years if requested for revision.

**Table 1 Tab1:** Data collection flow chart

Timing	Method	Data type and specification
At screening	eCRF (RedCap)	Inclusion and exclusion criteria and informed consent
At randomisation	eCRF (RedCap)	Allocation, treatment limitations (i.e. ICU admission), weight, height, place of birth, smoking, date of symptom start, gender, clinical frailty scale, mode of respiratory support, SpO2%, litres O2/min, RR/min and NEWS
One hour post randomisation	CRF paper	SpO2/FiO2-ratio
24 h post randomisation	CRF paper	Patient comfort (visual analogue scale (VAS) 1–10)
Daily for 28 days	CRF paper	Mode of respiratory support, number of hours per 24 h in allocated support, nr of hours in prone position per 24 h, NEWS, PEEP or Flow, SpO2%, RR/min and events with commentary (e.g. allocation violation, death, exit from study, ICU admission or hospital discharge)
Retrospectively from electronic medical charts	eCRF (RedCap)	Comorbidities, vitals, medications, radiology, microbiology and laboratory parameters at triage, randomisation and during hospital stay, and, duration of hospital stay, duration of ICU stay, duration of mechanical ventilation and days alive within 28 and 180 days, respectively.

*Abbreviations*: *eCRF* electronic case report form, *ICU* intensive care unit, *SpO2%* peripheral oxygen saturation, *L O2/min* litres of oxygen per minute, *RR* respiratory rate, *NEWS* national early warning score, *FiO2* fraction of inspired oxygen, *PEEP* positive end-expiratory pressure

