### Methods for additional analyses (e.g. subgroup analyses) {20b}

Because baseline characteristics may be skewed between the two groups despite randomisation, we will also perform adjusted analyses for (a) the primary outcome of VFD using competing risks regression and (b) for the secondary outcome of 28- or 180-day survival using Cox regression. Since we are expecting only ~ 26 events (calculation: 60*(1/3*0.674 + 2/3*0.081) + 60*(2/15*0.674 + 13/15*0.081)), we are limited to few co-variates to avoid overfitting. We plan to adjust for age (cont.), Clinical Frailty Index (cont.) and NEWS score at randomisation (cont.). If other baseline characteristics appear severely skewed instead, we may consider adjusting for other co-variates, such as gender, comorbidities (Charlson comorbidity index), BMI, smoking, Nordic origin of birth or serum biomarkers (e.g. lactate, serum D-dimer, lymphocyte count).

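### The 1 h SpO2/FiO2 ratio is compared by a valid but unadjusted Mann-Whitney test, although SpO2 and oxygen flow are recorded at randomisation and could be used at no cost to gain precision

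*Protocol article*

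**What the plan says.** In the protocol article, the Secondary outcomes paragraph of section {20a} fixes the analysis: "SpO2/FiO2 ratio (a) and patient comfort (b) will also be analysed as continuous outcomes between two groups". The test it names is Mann-Whitney, and it gives no covariate for either outcome.

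Table 1, under Data management {19}, lists among the items entered in the eCRF at randomisation "gender, clinical frailty scale, mode of respiratory support, SpO2%, litres O2/min, RR/min and NEWS". Two direct measures of baseline oxygenation, SpO2 and oxygen flow, are therefore available for this analysis. FiO2 at baseline is not listed.

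The section Outcomes rational gives the outcome its role. It is "included as a sort of proof of concept outcome with the purpose of confirming or rejecting our underlying assumption", namely that the higher PEEP possible with the helmet improves lung aeration.

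Section {20b} does plan adjustment, and gives its reason: "Because baseline characteristics may be skewed between the two groups despite randomisation". Only VFD and survival (to 28 or 180 days) are named there as receiving it. The 1 h ratio is not among them, and the planned covariates are age, frailty and NEWS, not SpO2 or oxygen flow as such.

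**The concern.** Oxygenation one hour after randomisation may well be related to oxygenation at randomisation. If it is, a comparison that ignores the baseline values has a wider error than it needs, and a chance difference between the arms at baseline carries partly into the 1 h comparison. Randomisation is blocked but unstratified (section {16a}), with 60 patients per arm, so the design does nothing to balance baseline oxygenation.

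The protocol gives chance imbalance as its reason for adjusting VFD and survival. The same reason applies to a physiological measure taken one hour after randomisation. What is at stake is how clearly the trial can speak to its mechanism: an imprecise comparison, or one shifted by baseline imbalance, is a weaker test of the assumption about PEEP.

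**Working it through.** **Inputs from the protocol article.** 60 per arm, 1:1, two-sided 0.05 (Trial design {8}, Sample size {14}). The article states no effect size, SD or power for SpO2/FiO2 and no correlation between baseline and 1 h values.

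**Assumptions.** rho is the (multiple) correlation of the baseline covariates with the 1 h ratio, ranged from 0 to 0.7. The true difference is set at 0.45 SD for illustration. Data are normal.

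**Step 1: reproduce the plan's own figure.** This checks the method on the primary outcome. The difference is 23.257 − 19.545 = 3.712, with SD 6 and 90% power. Then n = 2 × (1.96 + 1.2816)² × 6² / 3.712² = 54.9, so 55 per arm. Dividing by the Mann-Whitney efficiency 3/π gives 57.6, so 58. Simulation with normal data (20,000 runs) gives 90.7% power at 60 per arm. The stated 60 per arm is reproduced.

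**Step 2: precision.** Adjustment leaves a fraction 1 − rho² of the variance, so 60 per arm is worth 60 / (1 − rho²).

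**Step 3: power, rank test against rank ANCOVA.** Power = Φ(0.45 × √(m/2) − 1.96), with m = 60 × (3/π) / (1 − rho²). At rho = 0, m = 57.3, and this is the Mann-Whitney power.

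**Step 4: imbalance carried over.** The 95% range of a chance baseline difference is ±1.96 × √(2/60) = ±0.36 baseline SD. Without adjustment, rho times this enters the 1 h difference.

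| rho | Variance left | Equivalent n per arm | m | Power, rank ANCOVA | Shift at edge of 95% range (SD) |
|---|---|---|---|---|---|
| 0 | 100% | 60 | 57.3 | 67% (as Mann-Whitney) | 0 |
| 0.2 | 96% | 62.5 | 59.7 | 69% | 0.07 |
| 0.3 | 91% | 66 | 63.0 | 71% | 0.11 |
| 0.5 | 75% | 80 | 76.4 | 79% | 0.18 |
| 0.7 | 51% | 118 | 112.3 | 92% | 0.25 |

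These powers are large-sample approximations. Simulating the same setting (20,000 runs) gives values one to two points lower for both tests, so the comparison is unchanged.

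**Step 5: check by simulation at another effect size.** At 0.52 SD, where Mann-Whitney has about 80% power, rank ANCOVA gave about 80% / 82% / 89% / 97% for rho 0.2 / 0.3 / 0.5 / 0.7 (6,000 runs).

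**Step 6: validity of the planned test.** In the same simulations with no true difference, the Mann-Whitney test rejected in 4.7% to 5.3% of trials. Among trials with a baseline imbalance above 1.5 standard errors in either direction, it rejected in about 5% / 7% / 14% / 19% for rho 0.2 / 0.3 / 0.5 / 0.7, against about 4% to 6% with ANCOVA.

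**The case against.** The strongest reply is that nothing here is wrong. The Mann-Whitney test is a standard test for two randomised groups, the outcome is secondary, and an unseen analysis plan might add an adjusted analysis. The first two statements are true, and they limit the weight of the point. The third does not remove it: the article states the test and lists the outcomes that will be adjusted, so this is a choice made in the text.

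The second reply is that rho may be low. Entry requires SpO2 below 92% on at least 6 L/min (section {10}), which narrows the range of baseline SpO2. Local guidance has a target SpO2 of 92%, and oxygen settings follow the physician's choice (section {11a}), so the 1 h ratio may largely reflect the FiO2 chosen. The device also changes at randomisation. This stands, and it is why the range must include 0 to 0.2, where there is little or nothing to gain. On the other side, baseline oxygen flow has a floor but no stated ceiling, so it may still be informative.

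Three stronger readings are tempting, and the documents do not support them.

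- A reader might infer that the comparison is biased or falsely confirms the mechanism too often. Over all randomisations it does not; the excess appears only among trials that happen to be imbalanced, and it grows with rho.
- A reader might infer that the 1 h ratio is known to depend strongly on baseline hypoxaemia. The article gives no figure for this.
- A reader might quote a power gain from 67% to 73%, 81% or 93% at rho 0.3, 0.5 or 0.7. That compares a rank test with parametric ANCOVA, and about two points of each gain come from dropping ranks, not from using baseline.

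Two practical objections fail. A missing baseline FiO2 does not prevent adjustment, because SpO2 and flow can enter as separate covariates. The limit of about 26 events in section {20b} concerns event-based models; it does not bind a continuous outcome in 120 patients, where the adjustment costs two degrees of freedom.

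**Conclusion.** The point holds as a free improvement, not as an error. The planned test is valid but less efficient than one that uses baseline values already collected, and it leaves chance imbalance in the estimate in proportion to rho. The direction is certain for any appreciable rho; the size is not, because rho and the effect of 0.45 SD are assumptions. On those assumptions the like-for-like gain in power is about 4, 12 and 25 points at rho 0.3, 0.5 and 0.7, and negligible at 0.2 or below. It concerns one secondary, proof-of-concept outcome.

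**What to change.** In the Secondary outcomes paragraph of section {20a}, give the 1 h SpO2/FiO2 ratio its own sentence. Its main analysis would be an ANCOVA on arm, with SpO2% and litres O2/min at randomisation as separate covariates, rank-based if the distribution is skewed. Report the adjusted difference with its 95% confidence interval. Keep the unadjusted Mann-Whitney test as a sensitivity analysis. State in advance how skewness will be judged, for example on the pooled data without the allocation code.

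The cost is one sentence and one extra model. No new data are needed. Outcome data are entered after recruitment ends (section {19}) and the statistician is blinded to allocation (section {17a}), so the change can be specified before any comparison of the arms is seen.

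### The carbon dioxide rebreathing comparison ignores each patient's starting pCO2 and so loses sensitivity for the main device-specific harm; it does not create a false helmet signal

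*Protocol article*

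**What the plan says.** All references are to the protocol article.

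- **Eligibility criteria {10}** excludes patients whose pCO2 in a venous blood gas (VBG) is above 6 kPa.
- **Outcomes {12}** defines rebreathing as a VBG pCO2 above 6 kPa within 28 days of randomisation. The limit and the sample type are the same as at entry.
- **Statistical methods {20a}, Secondary outcomes** fixes the comparison: "Frequency of endotracheal intubation (c) and carbon dioxide rebreathing (d) are dichotomized outcomes between two groups and will be analysed using a chi-squared test", with Fisher's exact test for small groups. No covariate is named.
- **Methods for additional analyses {20b}** plans adjusted analyses for VFD and survival only, with age, frailty and NEWS. pCO2 is not named, even among the optional covariates.
- **Data management {19}, Table 1** lists retrospective collection of "laboratory parameters at triage, randomisation and during hospital stay". The fields entered at randomisation do not name pCO2.
- **Outcomes rational** says that rebreathing "is the main harm apart from death and comfort/tolerance issues that can be considered more likely for the intervention group than the control group".

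**The concern.** The distance to the limit varies between patients. One who enters at 5.9 kPa becomes an event after a rise of just over 6 − 5.9 = 0.1 kPa; one who enters at 4.5 kPa must rise by more than 6 − 4.5 = 1.5 kPa. Starting pCO2 therefore partly decides who is an event, and the planned test treats that known variation as noise.

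This matters because of the outcome's role. Adverse event reporting and harms {22} relies on the listed endpoints, rebreathing among them, to evaluate harm. Interim analyses {21b} and the data monitoring committee section {21a} plan neither an interim look nor a committee. A non-significant result from an insensitive test could be read as reassurance about the helmet.

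**Working it through.** **1. The plan's own figure.** The only power statement concerns VFD: "We have estimated a required sample size of 120 patients (60 per group) to achieve 90% power". Its inputs are a two-sided 0.05 level, means of 23.257 and 19.545 (difference 3.712) and an SD of 6.

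- Normal-theory size per arm: 2 × (1.960 + 1.282)² × 6² / 3.712² = 54.9, so 55.
- Mann-Whitney efficiency: 55 × π/3 = 57.6, so 58.
- Simulated Mann-Whitney power with normal data: 0.899 at 58 per arm and 0.907 at 60.

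The stated 60 per arm reproduces. No rate, effect or power is given for rebreathing, so 60 per arm is simply what is available for it.

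**2. What an unadjusted test can detect with 60 per arm.** The rates are assumed. Power = Φ[(|p1 − p0| − 1.96 × √(2p̄(1 − p̄)/60)) / √((p0(1 − p0) + p1(1 − p1))/60)].

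- 10% v 20%: (0.100 − 1.96 × 0.0652)/0.0645 = −0.43, power 0.33.
- 5% v 15%: (0.100 − 1.96 × 0.0548)/0.0540 = −0.14, power 0.45.
- 10% v 30%: power 0.79. 30% v 60%: power 0.92.

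**3. Crossings with no device effect.** Model, assumed: measured baseline = true level + noise, kept only if at or below 6 kPa; later samples = true level + shift + noise.

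| Assumed setting | VBGs per patient | Share of each arm above 6 kPa, no shift |
|---|---|---|
| mean 5.0-5.4, between-patient SD 0.5-0.6, within-patient SD 0.3-0.4 | 3 | 6-23% |
| mean 4.8-5.6, SDs 0.6 and 0.5 | 1 | 4-19% |
| mean 4.8-5.6, SDs 0.6 and 0.5 | 5 | 15-47% |

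In the second and third settings, about 38-59% of these events come from patients who entered above 5.5 kPa. They fall equally on both arms, and the chi-squared rejection rate under no effect is 0.043-0.058.

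**4. Same binary outcome, with and without baseline.** Assumed: mean 5.0-5.4 kPa, between-patient SD 0.5-0.6, within-patient SD 0.3-0.5, three VBGs, 60 per arm, helmet shift +0.3 kPa.

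| Analysis of pCO2 above 6 kPa | Power |
|---|---|
| Chi-squared or Fisher, unadjusted | about 0.43-0.77 |
| Logistic regression with baseline pCO2 | about 0.52-0.87 |

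The ends of the ranges differ by 0.52 − 0.43 = 0.09 and 0.87 − 0.77 = 0.10. The gain is largest when within-patient variation is small. A repeat with a penalised fit and a Wald test showed the same pattern, with little gain at the top of the assumed within-patient range.

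**5. Changing the outcome is a different matter.** For the same shift, with within-patient SD 0.3-0.4, a linear model of the first later sample has power 0.70-0.90 without baseline and 0.88-0.99 with it. With between- and within-patient SDs of 0.6 and 0.5 and one VBG, the baseline-adjusted linear model has 0.73-0.74. Much of this gain comes from testing a mean shift instead of crossings of 6 kPa, so it cannot all be credited to the baseline covariate.

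**The case against.** **The planned test is valid.** This stands. A reader might infer that ordinary drift in patients just under 6 kPa will be counted against the helmet. The documents do not support that: drift is labelled rebreathing in both randomised arms, and with equal sampling the test keeps its size.

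**The shared limit is sensible.** This also stands. Objectives {7} asks for the relative incidence of rebreathing. Excluding patients already above 6 kPa means nobody is an event at entry.

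**The lost power is assumed.** Largely so. A reader might conclude that a real helmet effect will easily be missed. The article gives no pCO2 mean, SD, number of samples or device effect, and the planned test's power runs from about 0.2 to above 0.9 over plausible inputs. The direction is firmer than the size.

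**A linear model would not answer the same question.** This stands. A mean rise below 6 kPa is not the harm that the article defines. Table 1 shows no fixed VBG time, and patients without a later sample drop out, which sits badly with the as-randomised analysis. It can only be supportive.

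**Baseline pCO2 is probably collected anyway.** Probably: Table 1 covers laboratory values at randomisation. Nothing shows that the value is lost; it is just not named or used.

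**Covariate choice belongs in the analysis plan.** Only in part. An analysis plan may exist, but the article itself names the test and says which outcomes get adjusted analyses. The point changes a stated method.

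**Larger threats lie elsewhere.** True, and baseline adjustment does not cure them. Any VBG in 28 days counts, on or off the device. With no true effect, eight VBGs per helmet patient against three per control patient would raise the chi-squared false-positive rate to 0.26-0.43 (assumed means 4.8-5.2 kPa, SDs 0.6 and 0.5).

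**Conclusion.** The point holds as a loss of efficiency. The planned comparison is unbiased under equal sampling, but it discards a baseline value that eligibility already requires, for the outcome that the article singles out as the main harm beyond death and comfort or tolerance. Under the assumptions in step 4, adjusting the same binary outcome raises power from about 0.43-0.77 to about 0.52-0.87. That gain is modest and depends on within-patient variation. The primary analysis and the sample size are unaffected. The change is worth making because it is cheap, but it does not remove the need to read a non-significant result with caution.

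**What to change.** In Statistical methods {20a}, Secondary outcomes:

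1. Keep the frequency of VBG pCO2 above 6 kPa as the outcome and report it by arm.
2. Replace the chi-squared or Fisher test for this outcome with logistic regression on arm and baseline VBG pCO2 (continuous). Use a penalised fit, since events may be sparse, and give the odds ratio with a 95% CI.
3. Add, as a supportive analysis only, a linear model of on-device pCO2 adjusted for baseline, with the difference in kPa and its 95% CI. State how many patients per arm lack a later on-device VBG.

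In Data management {19}, Table 1, name the baseline VBG pCO2 value as an eCRF field at screening or randomisation.

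Cost: one field for a value already measured, and a slightly more complex analysis. The odds ratio becomes conditional on baseline pCO2, so the frequencies by arm must stand beside it to answer the stated objective.
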